# Detection of occult paroxysmal atrial fibrilation by implantable long-term electrocardiographic monitoring in cryptogenic stroke and transient ischemic attack population: a study protocol for prospective matched cohort study

**DOI:** 10.1186/s12872-015-0160-8

**Published:** 2015-12-03

**Keywords:** Transient ischemic attack, Cryptogenic stroke, Atrial fibrillation, Implantable loop recorder, PITX2, ZFHX3

## Abstract

**Background:**

Cardio-embolic etiology is the most frequently predicted cause of cryptogenic stroke/TIA. Detection of occult paroxysmal atrial fibrillation is crucial for selection of appropriate medication.

**Methods:**

Enrolment of eligible cryptogenic stroke and TIA patients began in 2014 and will continue until 2018. The patients undergo long-term (12 months) ECG monitoring (implantable loop recorder) and testing for PITX2 (chromosome 4q25) and ZFHX3 (chromosome 16q22) gene mutations. There will be an appropriate control group of age- and sex-matched healthy volunteers. To analyse the results descriptive statistics, statistical tests for group differences, and correlation analyses will be used.

**Discussion:**

In our study we are focusing on a possible correlation between detection of atrial fibrillation by an implantable ECG recorder, and PITX2 and/or ZFHX3 gene mutations in cryptogenic stroke/TIA patients. A correlation could lead to implementation of this genomic approach to cryptogenic stroke/TIA diagnostics and management. The results will be published in 2018.

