## Background

Stroke has consistently been the 2^nd^ leading cause of death in the age group of 60 plus worldwide [1]. Recently, it has become the 4^th^ leading cause of death and the 1^st^ leading cause of serious long-term disability in the USA [2]. Accurate definition of stroke etiology is crucial for the most effective management of the disease.

Cryptogenic stroke (CS), according to the TOAST classification, is defined as an ischemic stroke with undeterminable etiology, despite extensive evaluation [3]. Stroke might be cryptogenic for several reasons: 1) evaluation is not carried out at the time of event; 2) investigation is not sufficiently extensive; or 3) there are other unknown causes. Therefore the proportion of CS depends on the speed and wider-than-routine range of diagnostic evaluation. Epidemiological observational trials using standardized stroke etiological classification report 20–40 %, in some cases up to 50 % incidence of unrevealed causes [4–6].

Cardio-embolic stroke is the most frequently predicted cause of CS in studies (58 %) [7, 8]. The most frequent cause of cerebral cardio-embolism, as well as the most common cardiac arrhythmia, is atrial fibrilation (AF). The incidence of stroke in people with non-valvular AF is estimated to be 5 times higher than in people without AF [9]. It has been suggested that paroxysmal AF (PAF) is more prevalent than chronic AF in stroke and TIA patients, and they both appear to carry very similar stroke risk [10].

Episodes of PAF may reoccur with variable frequency and their detection has been made possible by ECG monitoring. Short and usually asymptomatic presentations of PAF (also occult PAF) may remain undetected by routine arrhythmia screening methods. Incidence of newly identified PAF varies widely depending on the type of cardiac monitoring devices, the delay in monitoring after stroke onset and the monitoring duration. Detection rate of PAF with external ECG monitoring in patients after CS has been recorded between 5 and 20 % [11–13]. An insertable cardiac monitor (ICM) automatically provides non-stop long-term ECG recording with very high sensitivity and specificity for PAF detection. Studies using ICM have suggested a detection rate of approximately 25 % [14–16].

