### Study participants

The study will analyse data from at least 100 patients with CS or CTIA admitted to the Department of Neurology in Nitra between 2014 and 2018 as well as at least 30 age- and sex-matched volunteers with no known vascular diesease in the control group. The study protocol has been approved by the Ethics Committee of the Faculty Hospital in Nitra (Slovak Republic). A written informed consent will be obtained from all study participants or their legal representatives.

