### Imaging and laboratory testing

Stroke diagnosis is accepted only when supported by consistent findings on CT and/or MRI. To identify the location and size of ischemic infarction, and to exclude intracranial hemorrhage or other pathology, standard non-contrast CT examination is performed initially after stroke symptom onset. When convincing lesions are not visible on CT, the patients undergo brain MRI (including DWI) to confirm ischemic etiology. Following extensive imaging and laboratory testing, we are using the TOAST criteria to classify the stroke as cryptogenic. Only TIA patients with symptoms of speech problems, limb weakness or hemianopia (ABCD^2^ score) are considered and enrolled when CTIA is confirmed. To detect PAF, patients undergo 48-h ECG Holter monitoring within 7 days after stroke/TIA onset and only those without documented AF have implanted the ICM device (REVEAL XT, REVEAL LINQ, Medtronic Inc., Minneapolis, USA). Both patient and control groups are monitored for 12 months. Patients’ follow-up visits are scheduled 1, 6, and 12 months after stroke/TIA onset and every 6 months thereafter until clinical study closure with extra visits in case of any new stroke/TIA symptoms. Disability of patients is classified according to the mRS and Barthel Index score. The healthy control participants undergo assessment at visit scheduled 1, 6, and 12 months after the implantation. Except standard blood laboratory analysis, complete vasculitis and thrombophilia testing panels are performed. Analysis of PITX2 (chromosome 4q25) and ZFHX3 (chromosome 16q22) gene polymorphisms are evaluated by PCR with genetic variation analysis such as restriction analysis (RFLP), high resolution melting (HRM), or allele-specific PCR. To analyse the data, descriptive statistics, statistical tests for differences, and correlation analyses will be used. This prospective and observational study is registered at www.clinicaltrials.gov with study identifier NCT02216370.

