## Discussion

Unrecognized PAF and the consequent lack of prophylactic anticoagulant treatment may result in significant morbidity first presenting as a heart failure, stroke, systemic embolism, and occasionally death. It is generally accepted that intermittent ECG monitoring (Holter ECG) has low sensitivity to identify patients with PAF. The commonly used 24-h Holter ECG monitoring has been found to reach PAF diagnostic sensitivity of 2.4–9.4 % [19–21]. Longer continuous non-stop ECG monitoring has been shown to increase PAF detection. In a sub-study of TRENDS, a single 24-h Holter ECG diagnosed PAF in 3 %, whereas 7, 21, or 30 days of monitoring diagnosed PAF in 6, 9, or 11 %, respectively [22]. The EMBRACE study (The 30-Day Cardiac Event Monitor Belt for Recording Atrial Fibrillation After a Cerebral Ischemic Event) used noninvasive ambulatory ECG monitoring in patients with cryptogenic stroke or TIA for 30 days. Detection of atrial fibrillation improved fivefold and indication of anticoagulant treatment nearly doubled when compared with standard practice of short-duration ECG monitoring. AF was detected in 16.1 % of patients in the intervention group, compared with 3.2 % in the control group [23]. ICM devices for long-term ECG monitoring have been used primarily for differential diagnosis of syncope [24]. Cotter et al. reported “Reveal XT” PAF identification in 25.5 % (13 patients) of 51 patients with unexplained stroke [14]. Sensitivity and specificity of “Reveal XT” device for PAF was detected to be 96.1 and 85.4 % respectively (3-year non-stop monitoring) [25]. A large randomized clinical trial The Cryptogenic Stroke and Underlying Atrial Fibrillation trial (CRYSTAL AF) compared long-term ECG monitoring by ICM with conventional ECG Holter monitoring in patients with recent CS. After 12 months ICM monitoring detected over 7 times more patients with PAF than ECG Holter monitoring. Three-year follow-up detected 30 % PAF occurrence in the ICM group compared to 3 % in the Holter group [26]. Choe evaluated sensitivity and negative predictive value (NPV) of various external monitoring techniques in a cryptogenic stroke cohort. Simulated intermittent monitoring strategies were compared with continuous rhythm monitoring in 168 ICM patients of the CRYSTAL AF trial. Short-term monitoring included a single 24-h, 48-h and 7-day Holter, and 21-day and 30-day event recorders. Periodic monitoring consisted of monthly monitoring by 24-h Holters and quarterly monitoring by 24-h, 48-h and 7-day Holters. For a single monitoring period, sensitivity for AF diagnosis was lowest with 24-h Holters (1.3 %) and highest with 30-day event recorders (22.8 %). NPV ranged from 82.3 to 85.6 % for all single external monitoring strategies. Quarterly monitoring with 24-h Holters had 3.1 % sensitivity, whereas quarterly 7-day monitors increased it to 20.8 %. NPV of various types of repetitive periodic monitoring were similar at 82.6 to 85.3 %. Long-term continuous monitoring was superior in detecting AF compared to all types of intermittent monitoring evaluated (p <0.001) [27]. Ritter et al. presented 17.0 % PAF detection in ICM group in comparison with 1.7 % in 7-day ECG Holter group (p = 0.0077) [28].

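### A correlation between PITX2/ZFHX3 variants and ICM-detected PAF would not by itself support diagnostic use; the genetic result should be given as diagnostic accuracy against the ICM

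*Protocol article*

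**What the plan says.** The Discussion paragraph of the Abstract and the last paragraph of the Background both name the correlation between ICM-detected AF and PITX2 and/or ZFHX3 variants as the focus. Both then state the use it might lead to: "A correlation could lead to implementation of this genomic approach to cryptogenic stroke/TIA diagnostics and management". The Conclusion foresees the genes helping to pick out people at high risk of PAF for extensive ECG monitoring.

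On analysis, Imaging and laboratory testing says that "descriptive statistics, statistical tests for differences, and correlation analyses will be used"; the Abstract's Methods paragraph says much the same. Objective and endpoints gives the objective as the proportion of patients with PAF compared with controls. Its genetic primary endpoint is the incidence of the mutations. No accuracy measure is attached to genotype.

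For ECG monitors, by contrast, the Discussion cites sensitivity and negative predictive value against continuous ICM recording, for example "NPV ranged from 82.3 to 85.6 % for all single external monitoring strategies".

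The planned size is "at least 100 patients with CS or CTIA admitted to the Department of Neurology in Nitra between 2014 and 2018" and "at least 30 age- and sex-matched volunteers with no known vascular diesease in the control group".

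**The concern.** Using a genotype in diagnostics, or to choose who is monitored, is a classification task. What matters is how many PAF patients carry the variant, how many non-PAF patients also carry it, and how far a negative result changes the chance of PAF. A correlation coefficient or a p-value answers none of these. An association can be real and statistically significant while a large share of PAF patients are non-carriers.

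Correlation is the only route to clinical use that the article names, so a positive result could be read as going further than it does. Patients who enter ICM follow-up are also genotyped, so the reference standard needed for accuracy measures is already in the design.

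**Working it through.** **Figures in the article.** The sample size of 100 and 30 is stated without alpha, power, effect size or carrier frequency, so it cannot be reproduced. The cited "PAF identification in 25.5 % (13 patients) of 51 patients with unexplained stroke" checks: 13/51 = 25.5%.

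**Inputs**
- PAF rate p = 25%, from the Background: "Studies using ICM have suggested a detection rate of approximately 25" per cent. Lower and higher rates in the Discussion are 17% ("17.0 % PAF detection in ICM group") and 30% (at three years).
- Carrier frequency f = 20–40% among all patients: assumed.
- Odds ratio (OR) 1.5–3: assumed.
- Two-sided alpha 0.05: assumed.

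**Step 1: accuracy implied by an association.** Let p1 and p0 be the PAF risk in carriers and non-carriers. Solve

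(1 − f)·p0 + f·p1 = p, with p1/(1 − p1) = OR · p0/(1 − p0).

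Then PPV = p1, NPV = 1 − p0, sensitivity = f·p1/p, and specificity = (1 − f)(1 − p0)/(1 − p).

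Worked case, p = 0.25, f = 0.30, OR = 2: p0 = 0.209 and p1 = 0.346 (check: 0.7 × 0.209 + 0.3 × 0.346 = 0.250).
- Sensitivity = 0.3 × 0.3457/0.25 = 41.5%, so 58.5% of PAF patients are non-carriers.
- Specificity = 0.7 × 0.791/0.75 = 73.8%.
- PPV = 34.6%; NPV = 79.1%.

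Corners of the grid at p = 25% (no-test PAF-free rate 75%):

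| Carriers | OR | Sensitivity | Missed | Specificity | PPV | NPV |
|---|---|---|---|---|---|---|
| 20% | 1.5 | 25% | 75% | 82% | 31% | 77% |
| 20% | 3 | 35% | 65% | 85% | 43% | 80% |
| 40% | 1.5 | 47% | 53% | 62% | 30% | 78% |
| 40% | 3 | 60% | 40% | 67% | 38% | 83% |

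The same formulas at the other PAF rates give 38–74% missed and NPV 84–89% (no test: 83%) at p = 17%, and 41–75% missed and NPV 72–79% (no test: 70%) at p = 30%.

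**Step 2: can this coexist with a significant result at the planned size?** 100 patients at 25% PAF give 25 PAF and 75 non-PAF patients. Assume carriers in 13/25 and 19/75:
- phi = (13 × 56 − 12 × 19)/√(32 × 68 × 25 × 75) = 0.25; Fisher exact p = 0.024.
- Sensitivity 13/25 = 52% (95% Clopper–Pearson interval 31–72%), so 12 of 25 (48%) are missed.
- Specificity 56/75 = 75%; PPV 13/32 = 41%; NPV 56/68 = 82%, against 75% with no test.

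The odds ratio in that table is (13 × 56)/(12 × 19) = 3.19, just above the assumed range. A table inside the range shows the same: 12/25 against 18/75 has OR (12 × 57)/(13 × 18) = 2.92, Fisher p = 0.042 and 52% missed.

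**Step 3: dependence on carrier frequency.** The smallest number of PAF carriers that gives Fisher p < 0.05 with 25 and 75 patients:

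| Carriers among non-PAF | Sensitivity at threshold | Missed |
|---|---|---|
| about 10% | 28% | 72% |
| about 20% | 44% | 56% |
| about 25% | 48% | 52% |
| about 30% | 56% | 44% |
| about 40% | 68% | 32% |
| about 50% | 76% | 24% |

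**The case against.** The best defence is that the article claims little. The wording is conditional, it sits in the Abstract's Discussion and the Background, and no text sets a correlation as a threshold for adoption. An association study that prompts later diagnostic work is an ordinary sequence. The article is also a condensed account: the full protocol and any SAP are not shown, and descriptive statistics could include a table of sensitivity and specificity. Most of this stands. It rules out saying that the accuracy measures are absent from the full plan, or that the design cannot yield them. It does not remove the point that correlation is the only property the article links to diagnostic use.

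A reader might infer that the trial would not answer its own question. The documents do not support that: the stated objective is the PAF proportion against controls, and a correlation analysis does answer whether a correlation exists.

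A reader might also infer that genotype could do no better than the external monitoring the Discussion describes. That fails on sensitivity: 25–60% under the assumptions here, against 1.3–22.8% for single external monitoring periods. On NPV there is at most an overlap. With specificity taken as 1, the cited pairs imply a prevalence of (1 − NPV)/(1 − NPV × sensitivity): 0.177/(1 − 0.823 × 0.013) = 17.9%, and 0.144/(1 − 0.856 × 0.228) = 17.9%. At that prevalence genotype NPV would be 83.4–88.7%, against 82.3–85.6% for the monitors. Nor does the article reject Holter monitoring; it keeps a 48-hour Holter as the screen before implantation.

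Finally, the use foreseen in the Conclusion concerns people without cerebrovascular disease. Accuracy estimated in stroke and TIA patients would not carry over to them directly.

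**Conclusion.** The point holds in a limited form: a correlation alone does not support bringing genotype into stroke/TIA diagnostics, and the article offers no other basis. Under the assumed carrier frequencies and odds ratios, a real association leaves 40–75% of PAF patients undetected and raises the PAF-free probability after a negative result from 75% to only 77–83%. Specificity is about 62–85% and PPV about 30–43%. A nominally significant result at 100 patients is compatible with missing about half of PAF patients, but "about half" is not a figure from the documents. It applies when roughly 20–30% of non-PAF patients are carriers; over 10–50% the missed share at the significance threshold runs from 72% down to 24%. The weakness lies in the measure named, not in the data to be collected.

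**What to change.** In the Abstract's Discussion paragraph, the last paragraph of the Background, and Imaging and laboratory testing, state that the genetic result will be reported as sensitivity, specificity, PPV and NPV, each with a 95% confidence interval, of carrier status against ICM-documented PAF in the patient group. Do this for each gene and for either gene. Place the no-test PAF-free rate of the same cohort beside the NPV. Describe a correlation alone as hypothesis-generating.

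The cost is wording plus one two-by-two table for each gene and one for either gene, from data already planned. The downside is a less favourable claim if a correlation is found but the predictive values barely move. The intervals will also be wide: with about 25 PAF patients, the one for sensitivity spans about 40 percentage points.

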**Trial registration:**

ClinicalTrials.gov: NCT02216370.

## Background

Stroke has consistently been the 2^nd^ leading cause of death in the age group of 60 plus worldwide [1]. Recently, it has become the 4^th^ leading cause of death and the 1^st^ leading cause of serious long-term disability in the USA [2]. Accurate definition of stroke etiology is crucial for the most effective management of the disease.

Cryptogenic stroke (CS), according to the TOAST classification, is defined as an ischemic stroke with undeterminable etiology, despite extensive evaluation [3]. Stroke might be cryptogenic for several reasons: 1) evaluation is not carried out at the time of event; 2) investigation is not sufficiently extensive; or 3) there are other unknown causes. Therefore the proportion of CS depends on the speed and wider-than-routine range of diagnostic evaluation. Epidemiological observational trials using standardized stroke etiological classification report 20–40 %, in some cases up to 50 % incidence of unrevealed causes [4–6].

Cardio-embolic stroke is the most frequently predicted cause of CS in studies (58 %) [7, 8]. The most frequent cause of cerebral cardio-embolism, as well as the most common cardiac arrhythmia, is atrial fibrilation (AF). The incidence of stroke in people with non-valvular AF is estimated to be 5 times higher than in people without AF [9]. It has been suggested that paroxysmal AF (PAF) is more prevalent than chronic AF in stroke and TIA patients, and they both appear to carry very similar stroke risk [10].

Episodes of PAF may reoccur with variable frequency and their detection has been made possible by ECG monitoring. Short and usually asymptomatic presentations of PAF (also occult PAF) may remain undetected by routine arrhythmia screening methods. Incidence of newly identified PAF varies widely depending on the type of cardiac monitoring devices, the delay in monitoring after stroke onset and the monitoring duration. Detection rate of PAF with external ECG monitoring in patients after CS has been recorded between 5 and 20 % [11–13]. An insertable cardiac monitor (ICM) automatically provides non-stop long-term ECG recording with very high sensitivity and specificity for PAF detection. Studies using ICM have suggested a detection rate of approximately 25 % [14–16].

In our study we are focusing on a possible correlation between detection of atrial fibrillation by implantable ECG loop, and PITX2 and/or ZFHX3 gene mutations in cryptogenic stroke/TIA patients. A correlation could lead to implementation of this genomic approach to cryptogenic stroke/TIA diagnostics and management [17, 18].

## Methods

### Objective and endpoints

The objective of our study is to determine the proportion of patients with CS or cryptogenic TIA (CTIA) that have underlying PAF in comparison with control group. PAF is defined as an episode of irregular heart rhythm without detectable P waves lasting more than 30 s. Primary endpoints are the first documented PAF episode after CS or CTIA and incidence of PITX2 and ZFHX3 genes mutation. Secondary endpoints include recurrent stroke or TIA, new ischemic lesions found by brain imaging (CT and/or MRI), the size of left atrium (TTE/TEE), and relevant treatment changes (e.g. oral anticoagulant drugs). The follow-up of patient and control groups will last 12 months.

### Study participants

The study will analyse data from at least 100 patients with CS or CTIA admitted to the Department of Neurology in Nitra between 2014 and 2018 as well as at least 30 age- and sex-matched volunteers with no known vascular diesease in the control group. The study protocol has been approved by the Ethics Committee of the Faculty Hospital in Nitra (Slovak Republic). A written informed consent will be obtained from all study participants or their legal representatives.

### Inclusion criteria

CS or CTIA within 72 h from symptom onsetAge ≥ 18 yearsCS: modified Rankin Scale (mRS) ≤ 4 at discharge (to ensure patient compliance)CTIA: ABCD^2^ score ≥ 4Ability and willingness of the patients or their legal representatives to understand the study instructions, both verbal and written, in accordance with ICH, GCP and legislation of the Slovak Republic

### Exclusion criteria

Known etiology of stroke/TIAUntreated hyperthyroidismMyocardial infarction within 1 month of stroke/TIA onsetCoronary bypass within 1 month of stroke/TIA onsetValvular disease requiring urgent surgeryDocumented AF or flutterPatent foramen ovalePermanent indication for oral anticoagulation therapyLong-term steroid therapy > 30 daysParticipation in another clinical trial aimed at experimental pharmacologic therapyChronic inflammatory disease (rheumatoid arthritis, inflammatory bowel diseases, lupus erythematosus etc.)Severe co-morbidity not compatible with 12 months follow-upPregnant and breastfeeding womenIndication for implantation of pacemaker, implantable cardioverter defibrillator or implantable pulse generator

### Imaging and laboratory testing

Stroke diagnosis is accepted only when supported by consistent findings on CT and/or MRI. To identify the location and size of ischemic infarction, and to exclude intracranial hemorrhage or other pathology, standard non-contrast CT examination is performed initially after stroke symptom onset. When convincing lesions are not visible on CT, the patients undergo brain MRI (including DWI) to confirm ischemic etiology. Following extensive imaging and laboratory testing, we are using the TOAST criteria to classify the stroke as cryptogenic. Only TIA patients with symptoms of speech problems, limb weakness or hemianopia (ABCD^2^ score) are considered and enrolled when CTIA is confirmed. To detect PAF, patients undergo 48-h ECG Holter monitoring within 7 days after stroke/TIA onset and only those without documented AF have implanted the ICM device (REVEAL XT, REVEAL LINQ, Medtronic Inc., Minneapolis, USA). Both patient and control groups are monitored for 12 months. Patients’ follow-up visits are scheduled 1, 6, and 12 months after stroke/TIA onset and every 6 months thereafter until clinical study closure with extra visits in case of any new stroke/TIA symptoms. Disability of patients is classified according to the mRS and Barthel Index score. The healthy control participants undergo assessment at visit scheduled 1, 6, and 12 months after the implantation. Except standard blood laboratory analysis, complete vasculitis and thrombophilia testing panels are performed. Analysis of PITX2 (chromosome 4q25) and ZFHX3 (chromosome 16q22) gene polymorphisms are evaluated by PCR with genetic variation analysis such as restriction analysis (RFLP), high resolution melting (HRM), or allele-specific PCR. To analyse the data, descriptive statistics, statistical tests for differences, and correlation analyses will be used. This prospective and observational study is registered at www.clinicaltrials.gov with study identifier NCT02216370.

